#### Relationship Dissolution

The approximate date and primary reasons for the relationship ending, including whether the reasoning is linked to study participation or intervention use, will be captured through the quantitative follow-up assessment or when the research staff contact participants, each month, to ensure that their contact information is current. To avoid intervention contamination and outcomes, couples who break up (ie, whose relationship has ended) during the pilot RCT will not be permitted to rejoin the study with a new partner. After completion of the pilot RCT, we will conduct a sensitivity analysis to quantitatively explore whether couples who break up comparatively differ from those who did not break up during the pilot RCT. Partners or couples’ data will still be used in the intention-to-treat analysis plan via the last observation carried forward method [55,57]. On the basis of the principal investigator’s prior intervention work with couples, we do not anticipate >5% of couples breaking up during the pilot trial. In the study by Mitchell [8] and another study involving couples [58], <5% of couples had ended their relationship while in the study, and none had reported their reasons as being associated with the study participation. In addition, the length of time that couples will wait before receiving the intervention is 3 months, which may further decrease the possibility of their relationship ending before receiving the intervention. For the reasons mentioned, we expect that the impact of couple dissolution will be minimal in creating systematically different samples between trial arms. However, we cannot predict the rate of relationship dissolution and will adjust analyses accordingly to account for any differences between trial arms and differences over time if observed.

#### Power, Sample Size, and Effect Size Estimations

All power calculations were performed with PASS 2020 [59]. For the couple-level analyses, with 60 couples randomized to 2 arms (30 couples in each), for outcome C, we will have 80% power to detect a difference of 0.75 SDs of the mean relationship functioning measure (large effect [60]) using a linear model. For the dichotomous outcomes A and B, we will have 80% power to detect an absolute difference of 35% between the intervention and delayed conditions using a chi-square test. Our power increases for the outcomes analyzed at the individual level, where the correlation between individuals within a dyad must be considered (ie, the interdependence of individuals nested within dyads). For the incidence rate of outcome D assuming Poisson distribution, 30 couples in each arm will have 80% power to detect a difference of 50% rate reduction in STI rate (including HIV) between the intervention and delayed conditions at 6 months assuming a within-pair coefficient of variation between clusters at 0.25 and the intraclass correlation coefficient as high as 0.1 (even higher ICCs do not reduce rate reduction measure in a significant or meaningful way magnitude wise). For all analyses, the α level was set at .05 with 95% CI. This is a feasibility and acceptability trial that is only powered to detect large effects; however, if effect sizes are lower than hypothesized, we will use that information to properly power a large-scale RCT.

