## Introduction

### Background

Peru, similar to much of Latin America, has a concentrated HIV epidemic, where cisgender, sexual minority men (SMM; ie, gay, bisexual, and other men who have sex with men) are the primary population affected by HIV. While estimates vary across studies, most studies estimate 10% of HIV prevalence [1,2]; recent incidence estimates continue to be high, estimating an incidence rate of >6 cases per 100 person-years [3]. While there have been fewer studies focusing on sexually transmitted infections (STIs), existing studies point to a similar epidemic pattern [4,5]. Furthermore, epidemiological estimates indicate that between 32% and 39% of new HIV infections among adult cisgender SMM occur within primary partnerships (ie, among male couples) [6].

Although couples have been considered an important population for HIV prevention, no interventions focusing on couples have been tested or implemented in Peru. In this context, same-sex couples (eg, sexual and gender minorities) remain unacknowledged by Peruvian law and exist within a context of limited social and societal support [7]. In addition, while the health system provides both antiretroviral therapy (ART) and pre-exposure prophylaxis (PrEP), couples have not been integrated into considerations of treatment as prevention or PrEP provision, apart from pregnant women with a partner who is living with HIV. In short, HIV prevention care efforts in Peru have exclusively been limited to individual-level measures.

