## Methods

### Trial Study Design

The study design for the P3 DHI is a 6-month pilot RCT with an unmatched delayed control condition of 3 months. The pilot RCT for the P3 DHI is registered on ClinicalTrials.gov (NCT05873855). Assessments will occur every 3 months after the baseline assessment (at 3 and 6 months). Participants (ie, couples) will initially be blinded to which randomized condition they receive for the pilot RCT. Most study participation activities, including recruitment, eligibility screening, consent, enrollment, assessments, intervention, and exit interviews will occur on Zoom (Zoom Video Communications). During the pilot trial, participants will also undergo in-person HIV and STI testing at a local community-based organization at baseline and month 6. The planned sample size for enrollment is 60 adult cisgender SMM couples. The planned sample size will be balanced by dyad HIV serostatus and stratified by trial arm (ie, 10 seroconcordant negative, 10 serodiscordant, and 10 seroconcordant positive couples per arm). Florida International University (FIU) and Universidad Peruana Cayetano Heredia’s respective institutional review boards have approved the study protocol and all associated study activities.

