#### Level 1: Individual Eligibility

Each individual participant within an adult cisgender SMM couple must meet the following individual-level eligibility criteria for the P3 pilot RCT: (1) currently identifies as male and was assigned male at birth (ie, cisgender); (2) be aged ≥18 years; (3) has access to a web-connected device (eg, smartphone, laptop, tablet, or computer); (4) lives in and plans to live in Lima, Peru, for the next 6 months; (5) reports being in a relationship with another cisgender, SMM partner and defines their partner as *someone they feel emotionally or romantically committed to above all others, such as a partner, husband, boyfriend, etc*.; (6) reports being in their relationship for a minimum of 3 months; (7) reports having had CAS with their relationship partner within the previous 3 months; (8) one of the relationship partners reports having had CAS with a casual sex partner in the same timeframe; (9) reports to having no history (ie, within prior 3 months and ever) of intimate partner violence; (10) reports not being coerced by their partner (or others) to participate in the study and related activities; (11) reports feeling safe in the current relationship to participate in the study and related activities; and (12) indicates willingness to test for HIV and other STIs at a local community–based organization at baseline and at 6 months after baseline.

Except for level 1 eligibility criterion number 8, individuals who do not meet all other above-mentioned criteria, will be deemed ineligible, thanked for their interest in the study, and provided a list of HIV and STI prevention resources and other health and relationship-oriented resources that are available in Lima, Peru. Individuals who meet all other criteria (other than number 8) will be prompted to complete an e-consent and enter complete contact information of themselves and their partner. Then, partner 2 will receive a study invite via WhatsApp, which will provide them with access to the eligibility screener and e-consent (if applicable). Level 2 eligibility criteria will automatically be evaluated once both partners complete the eligibility screener.

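### The 80% power claimed for a halved STI rate has no control rate behind it; the plan's other inputs imply about 1.8 infections per man-year, and delayed-arm access weakens the claim further

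*Protocol article*

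**What the plan says.** The section on power, sample size and effect size makes a separate power claim for infections: "30 couples in each arm will have 80% power to detect a difference of 50% rate reduction in STI rate (including HIV". The contrast is between the intervention and delayed conditions at 6 months, with alpha 0.05. The stated basis is "For the incidence rate of outcome D assuming Poisson distribution", with a "within-pair coefficient of variation between clusters at 0.25" and "the intraclass correlation coefficient as high as 0.1". No control-arm infection rate appears in that section, and no composite STI rate appears anywhere in the article.

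Three other parts of the article bear on the claim:

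- **Randomization:** the delayed arm can use P3 for the last 3 of the 6 months.
- **Pilot RCT Baseline and Follow-Up Measures:** biological testing for HIV, chlamydia, gonorrhea and syphilis takes place at baseline and month 6.
- **Aim 3 and Primary Analyses:** Aim 3 calls outcome D a count, and places the comparison of arms between baseline and month 3. Primary Analyses then tests outcome D, with A and B, by a one-degree-of-freedom chi-square on proportions of couples.

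**The concern.** A power figure for a rate ratio means nothing until the control rate is fixed, because the number of events determines the precision. The article gives the effect, the sample size, the clustering and alpha, but omits this one input and still states the power without condition. The remaining inputs can be solved for the rate they imply, and that rate is high.

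The sentence also treats the 6-month contrast as a full intervention-versus-none comparison, although half of the delayed arm's follow-up is with access to P3. And it describes a Poisson rate comparison where the plan's primary test is a couple-level chi-square.

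Two things are at stake. A non-significant infection result could be read as informative because the plan claimed 80% power. The figure could also be cited when the next trial is planned.

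**Working it through.** **Inputs from the article.** 30 couples per arm; rate ratio 0.5; 6 months; coefficient of variation k = 0.25; alpha 0.05; 1:1 allocation. Two men followed for half a year give y = 2 × 0.5 = 1 person-year per couple, so 30 per arm.

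**Assumption.** Two-sided testing; the article does not state sidedness for this outcome.

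**Formula** (Hayes–Bennett, for cluster rates):

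c = a + (z_α + z_β)² × [(L0 + L1)/y + k²(L0² + L1²)] / (L0 − L1)²

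Here a = 1 for an unmatched and 2 for a pair-matched design, and (1.96 + 0.842)² = 7.849. With L1 = L0/2, y = 1 and k² = 0.0625 this reduces to:

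c − a = 7.849 × (6/L0 + 0.3125)

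**Reproducing the 80%.** It cannot be reproduced forward, because L0 is missing. Solving for L0 at 80% power:

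- Unmatched: 29/7.849 = 3.695; 3.695 − 0.3125 = 3.382; L0 = 6/3.382 = **1.77** per man-year.
- Matched: 28/7.849 = 3.567; 3.567 − 0.3125 = 3.255; L0 = 6/3.255 = **1.84**.
- 37 couples per arm (the 74 enrolled, if split evenly), unmatched: 36/7.849 = 4.587; 4.587 − 0.3125 = 4.274; L0 = **1.40**.

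Over 30 person-years, 1.77 to 1.84 is about 53 to 55 infections among 60 control men, and about half that in the intervention arm.

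Other two-sided variants (no clustering, design effect 1.1, no small-sample term, log-rate and square-root tests) give 1.5 to 2.0. One-sided variants give 1.2 to 1.6. Simulating couple counts with gamma variation between couples at a rate of 1.8 gives 81–82% power.

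**Power at assumed control rates.** Power = Φ(√[29/(6/L0 + 0.3125)] − 1.96), with 30 couples per arm, unmatched, and the control arm untreated for all 6 months:

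| Control rate per man-year (assumed) | √ term | Power |
|---|---|---|
| 0.2 | 0.978 | 16% |
| 0.6 | 1.677 | 39% |
| 1.0 | 2.143 | 57% |
| 1.5 | 2.593 | 74% |
| 1.8 | 2.820 | 81% |

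**Delayed-arm access.** Assume that the 50% effect is immediate and full in both arms once P3 is available. With untreated rate L, the delayed arm averages (L + 0.5L)/2 = 0.75L over 6 months and the immediate arm 0.5L. The rate ratio is 0.5/0.75 = 0.67.

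At L = 1.8 the arm rates are 1.35 and 0.90. The variance term is 2.25 + 0.0625 × (1.8225 + 0.81) = 2.415, and √(29 × 0.45²/2.415) = 1.56. Power is Φ(1.56 − 1.96) = 34%, or 35% without the small-sample term. If 1.8 is instead the delayed arm's average over the whole 6 months, power is about 43%.

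**The planned test.** For a chi-square with n = 30 couples per arm, proportions p and p/2, and mean proportion p̄:

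Power = Φ{[(p/2)√n − 1.96√(2p̄(1 − p̄))] / √[p(1 − p) + (p/2)(1 − p/2)]}

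At p = 0.71, p/2 = 0.355 and p̄ = 0.5325, this is (1.944 − 1.383)/0.659 = 0.851, so power is 80%. About 71% of control couples would have to be affected. At p = 0.5, power is 52%; at p = 0.3 it is 28%.

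**The case against.** The strongest reply is that no arithmetic error has been shown. The missing rate is an input to a software calculation and may be in the full protocol, which is not at hand. The outcome is a composite of four infections in men selected for recent condomless sex, and one man can contribute more than one event. The article also says that this is a feasibility and acceptability trial powered only for large effects, and that the next trial will be planned from observed effect sizes. Enrolment and data collection are complete, so no design decision now turns on the sentence.

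Much of this stands. It limits the point to an unsupported claim and lowers its severity. It does not rescue the sentence, because the 50% reduction is itself the large effect for which 80% is claimed. Nor does an unstated high rate deal with delayed-arm access or the different planned test.

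Four stronger readings are tempting and are not supported:

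- **That the trial certainly lacks 80% power.** The article gives no composite STI rate, so it cannot show that 1.8 per man-year is not reached.
- **That the Background figure proves the rate is far too low.** The text "estimating an incidence rate of >6 cases per 100 person-years" concerns HIV alone and is no benchmark for the composite.
- **That power is 10–40% at any lower rate.** That band fits only assumed rates of about 0.1 to 0.6; power is 57% at 1.0 and 74% at 1.5.
- **That the remark "even higher ICCs do not reduce rate reduction measure in a significant or meaningful way magnitude wise" is plainly wrong.** It concerns the detectable reduction. With the control rate held fixed, no separate coefficient of variation and a design effect of 1 + ICC, that reduction moves from 50% at ICC 0.1 to 52%, 54% and 57% at 0.2, 0.3 and 0.5. The remark is defensible at moderate ICCs and arguable at 0.5.

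**Conclusion.** The point holds as a claim of power that the article does not support. The 80% is stated without condition, yet under two-sided testing it holds only if controls have about 1.8 infections per man-year, or about 1.4 with 37 couples per arm. It also requires that the control arm be untreated for all 6 months, which the design does not provide. With immediate and equal effects in both arms, power at an untreated rate of 1.8 falls to about 35%. The power statement also does not describe the couple-level chi-square that Primary Analyses specifies.

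All control rates used here are assumptions, and the dilution figure rests on an effect that starts as soon as access opens. A slower or smaller effect in the delayed arm would dilute the contrast less. Severity is moderate, because the article already presents the study as a pilot powered only for large effects.

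**What to change.** Withdraw the unconditional 80% statement for infections. Alternatively, state the control rate that it assumes and give its source. If a power statement is kept:

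- give power over a range of control rates, labelled as assumptions;
- base it on the analysis that will be run (the couple-level chi-square), or change the stated analysis to a rate comparison so that the two sections agree;
- allow for the delayed arm's access in months 3 to 6, and state the assumption about how quickly the effect appears.

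Add a sentence saying that the trial is not powered for infections and that incidence will be reported by arm with 95% CIs. The ICC remark need not be deleted on these grounds.

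The cost is wording and a short recalculation. No data collection changes. The stated power becomes less favourable, or explicitly conditional.

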### Pilot RCT Baseline and Follow-Up Measures

Items about evaluation will only be assessed during follow-ups after the participants receive the intervention. All other measures, items, and scales will be assessed at each time point throughout the trial, including baseline. In addition to screening for inclusion, the eligibility screener will capture a variety of demographic information from each participant including age, race, sex at birth, gender identity, sexual identity, highest education attainment, current employment status, has a primary health care provider, relationship type, relationship length, couple cohabitation, and couple HIV serostatus. Other demographic information will be captured at each data collection time point (ie, at baseline, months 3 and 6) to assess participant’s current living arrangement, type of health insurance, affordability to pay for health care or medication costs when needed in the past 3 months, as well as whether participants were in a situation that required them to reduce a meal size or skip a meal because of not having enough money for food in the past 3 months (social determinants of health). Skip patterns will be used accordingly for baseline and follow-up assessments at months 3 and 6. Multimedia Appendix 1 [24,27-49] provides a brief description of all other items and scales that will be assessed at each time point and how they relate to the constructs of CIT-HBC [13,14].

Beyond the General Anxiety Disorder 2-item, 5 other items will be used to capture aspects about anxiety and worry specifically related to sex and being in a relationship. The items include the following: “Do you ever feel like you are walking on eggshells around your partner? (Yes, No, I don’t remember)”; “In thinking about the past 3 months, how much did you worry or feel anxious about having sex with your partner? (0=never to 4=always)”; “To what extent did this anxiety stop you from enjoying sex with your partner? (0=not at all to 2=a lot)”; “In thinking about the past 3 months, how much did you worry or feel anxious about having sex with others, not including your partner? (0=never to 4=always)”; and “To what extent did this anxiety stop you from enjoying sex with others, not including your partner? (0=not at all to 2=a lot).” Skip patterns will be used for the above set of items such that some items may not be displayed depending on the participant’s response to the previous item.

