Furthermore, some scales will be modified based on feedback from the Community Advisory Board and to help reduce time burden for participants. For instance, single global items from validated scales (eg, Dyadic Trust Scale [34] and Investment Model short form [36]) may alternatively be used to capture interpersonal trust, relationship commitment, and relationship satisfaction instead of the complete scale.

In addition to self-reports of partners using strategies over time, we will ask each participant to test for HIV and STIs at baseline and at 6 months post baseline by going to a local community-based organization. Biological data for new diagnoses of HIV, chlamydia, gonorrhea, and syphilis will be collected. For those previously diagnosed with syphilis, the rapid plasma reagin test will be processed to examine antibodies to syphilis. HIV will be assessed using a rapid test, with a rapid test from another manufacturer used as a confirmatory test if the first is positive. GeneXpert polymerase chain reaction testing will be used to diagnose chlamydia and gonorrhea infections.

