#### Aim 3: Preliminary Efficacy of the Intervention

Using the 6-month pilot RCT, this research will examine the preliminary efficacy of the intervention on couples: (A) formation and adherence to an HIV and STI prevention care plan containing evidence-based strategies (eg, ART for U=U, PrEP, and routine testing); (B) formation and adherence to a detailed sexual agreement, (C) relationship functioning (eg, mutual constructive communication and self-efficacy of decision-making and working together), and (D) self-reported and biomarker-confirmed indicators of vulnerability vis-à-vis sexual behaviors (eg, CAS) and HIV and STIs. The pilot RCT will have an allocation ratio of 1:1 and block randomization with a block size of 2, with blocks defined by dyad serostatus. Outcomes A and B will be dichotomous, outcome C will be continuous based on a bounded Likert scales, whereas outcome D will be a count variable based on STI incidence, HIV incidence, and CAS.

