## Discussion

### Principal Findings

This protocol describes the methods that will be used to conduct a 6-month pilot RCT to assess the feasibility, acceptability, and preliminary efficacy of P3, a couples-based DHI. Regarding feasibility, the enrolled sample exceeded the targeted sample size of 60 adult cisgender SMM couples by 23% (74/60), indicating a clear interest in this type of intervention and potential future public health service for the local population in Lima, Peru. Future findings from the trial will reveal details pertaining to which recruitment strategies worked best to reach the intended audience, how well the enrollment procedures worked, and the proportion of couples who were retained at the end of the 6-month pilot RCT along with reasons for attrition.

Findings relevant to the acceptability of P3 will be showcased using various data sources, all indicating whether couples deemed P3 to be acceptable as a couples-based DHI for meeting their prevention-care and relationship needs. Acceptability-related findings will also help describe potential areas to refine and improve P3.

It is anticipated that results from the pilot RCT will reveal the preliminary efficacy of the P3 DHI on couples’ formation and adherence to an HIV and STI prevention-care plan containing evidence-based strategies (eg, routine testing, PrEP, and ART for U=U), formation and adherence to a detailed sexual agreement, and their perceptions that their prevention-care plan and sexual agreement were in alignment. In addition, preliminary efficacy results will highlight whether couples’ relationship functioning, including mutual constructive communication and self-efficacy in working and making decisions together about their sexual health, improved over time. Finally, preliminary efficacy results will describe changes regarding partners’ and couples’ vulnerability to HIV and other STIs over time by analyzing self-reports of sexual behaviors (eg, CAS) and biomarker confirmation of test results.

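### The STI part of outcome D is powered as a 6-month incidence rate, but for chlamydia and gonorrhoea a single month-6 PCR measures positivity, and the planned test compares couple proportions

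*Protocol article*

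**What the plan says.** All references are to the protocol article.

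- **Definition.** Aim 3 describes outcome D as "self-reported and biomarker-confirmed indicators of vulnerability vis-à-vis sexual behaviors (eg, CAS) and HIV and STIs" and fixes its scale: "outcome D will be a count variable based on STI incidence, HIV incidence, and CAS".
- **Power.** Power, Sample Size, and Effect Size Estimations assumes a Poisson incidence rate for D and, with 30 couples per arm, claims "80% power to detect a difference of 50% rate reduction in STI rate (including HIV) between the intervention and delayed conditions at 6 months". The coefficient of variation between clusters is 0.25. No control rate is given.
- **Laboratory data.** Pilot RCT Baseline and Follow-Up Measures states "we will ask each participant to test for HIV and STIs at baseline and at 6 months post baseline". It adds "Biological data for new diagnoses of HIV, chlamydia, gonorrhea, and syphilis will be collected" and "GeneXpert polymerase chain reaction testing will be used to diagnose chlamydia and gonorrhea infections". There is no month-3 laboratory test.
- **Questionnaires.** The same section says "All other measures, items, and scales will be assessed at each time point throughout the trial, including baseline", apart from the evaluation items. The item list is in Multimedia Appendix 1, which is not at hand.
- **Test.** Primary Analyses compares the proportions of couples with outcomes A, B and D by a one-degree-of-freedom chi-square test, with a ratio of binomial proportions.
- **Losses.** Intention to Treat assigns an adverse outcome D to anyone lost to follow-up.
- **Discussion.** Principal Findings expects to describe vulnerability by "analyzing self-reports of sexual behaviors (eg, CAS) and biomarker confirmation of test results".

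**The concern.** An incidence rate needs each new infection in the period to be counted against the time at risk. One PCR at the end of 6 months does not do that for chlamydia or gonorrhoea. A man infected in month 1 and treated in month 2 is negative at month 6, although his six months still belong to the period the rate describes. What the laboratory delivers is positivity at month 6, which depends on both acquisition and duration of infection.

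Two things are at stake. First, the stated power for D refers to a quantity that the month-6 PCR does not measure and the chi-square test does not analyse. Second, duration is something the intervention may change, since routine testing is among the strategies it promotes. Earlier detection and treatment would lower month-6 positivity even with acquisition unchanged, and under the label of incidence that fall would be read as prevention. The pilot is also meant to inform the sizing of an efficacy trial.

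**Working it through.** **1. The plan's own figure.** Inputs from the power section: 30 couples per arm, rate ratio 0.5, k = 0.25, 80% power, α = 0.05 (two-sided assumed). The usual cluster formula for Poisson rates, with λ the control events per couple over 6 months, is

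c = 1 + (1.96 + 0.842)² × [(λ + 0.5λ) + k²(λ² + 0.25λ²)] / (0.5λ)².

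Setting c = 30 gives 29 = 7.849 × (6/λ + 0.3125), so λ = 6/3.382 = 1.77 events per couple in 6 months, or about 0.89 per man. The 80% can be neither reproduced nor refuted, because no control rate is stated. Other two-sided formulas give 1.57 to 1.84. On the formula above, power would be about 57% at 1.0 event per couple and about 34% at 0.5.

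**2. Share of infections still visible at month 6.** Assume constant acquisition and exponential time to clearance or treatment with mean d months. The visible share is f = (d/6)(1 − e^(−6/d)). If chlamydia and gonorrhoea are a share s of all events and every other event is seen, the missed share of the total is s(1 − f).

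| d (months) | f | missed, s = 0.5 | missed, s = 0.8 |
|---|---|---|---|
| 2 | 0.317 | 34% | 55% |
| 3 | 0.432 | 28% | 45% |
| 6 | 0.632 | 18% | 29% |
| 12 | 0.787 | 11% | 17% |

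Neither d nor s is in the documents. Both are assumptions.

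**3. Effect on the arm contrast.** If duration is equal in both arms, f cancels and the ratio is unbiased. If not, it is biased. One scenario: equal acquisition in both arms, background clearance with mean 12 months, and access to P3 moving every man at once from yearly to 3-monthly testing with treatment. The monthly removal hazard is 1/12 + 1/12 = 0.167 without P3 and 1/12 + 1/3 = 0.417 with it. Month-6 positivity, per unit acquisition rate:

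- Immediate arm: (1 − e^(−2.5))/0.417 = 2.20.
- Delayed arm, infections from months 3-6: (1 − e^(−1.25))/0.417 = 1.71.
- Delayed arm, infections from months 0-3: e^(−1.25) × (1 − e^(−0.5))/0.167 = 0.68. Arm total 2.39.
- Ratio: 2.20/2.39 = 0.92, with no effect on acquisition.

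**4. Power of the test actually planned.** For a chi-square test with n = 30 per arm and a halving (p₁ = p₀/2), power = Φ{[(p₀ − p₁) − 1.96·SE₀]/SE₁}, where SE₀ uses the pooled proportion and SE₁ the separate ones.

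- p₀ = 0.708, p₁ = 0.354: SE₀ = 0.129, SE₁ = 0.120, power 80%.
- p₀ = 0.50, p₁ = 0.25: power 52%.
- p₀ = 0.30, p₁ = 0.15: SE₀ = 0.108, SE₁ = 0.106, power 28%.

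**The case against.** The strongest reply is that this is only a label, because the primary analysis already compares proportions and no section states a person-time denominator for D. That is true of the test, and it makes the fix easy. It does not rescue the power statement, which is explicitly for a Poisson incidence rate.

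Self-report may recover some of what the laboratory misses. Aim 3 allows self-reported indicators of HIV and STIs, questionnaires are given at months 3 and 6, and an infection treated elsewhere will often have been diagnosed. This stands as a limit on the size. The sentence in Principal Findings links self-report with behaviours and biomarkers with test results, but it is a summary and does not exclude self-reported diagnoses. Infections that clear undiagnosed would still be missed.

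A reader might infer that the reported STI rate will be too low by 11-55%. The documents do not support that as a fact. The range rests on assumed durations and an assumed event mix. Infections persisting from baseline could be counted at month 6, and adverse-outcome assignment adds events: 6 of the 74 enrolled couples (8%) were not retained.

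A reader might also infer a large false effect. Against a control that never receives P3, the step 3 scenario gives 2.20/3.79 = 0.58, but that describes a hypothetical later trial. Here the delayed arm also receives P3 and the ratio is 0.92. Nor does the article say that the absolute STI rate will size the efficacy trial. It speaks of effect sizes.

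**Conclusion.** The point holds in a limited form. For chlamydia and gonorrhoea the laboratory part of D is month-6 positivity, while Aim 3 and the power section call it incidence and power it as a Poisson rate. That power line also does not match the chi-square test of couple proportions.

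The laboratory loss is about 11-55% if mean duration is 2-12 months, the two organisms are 50-80% of events, all other events are seen and self-report adds nothing. Its true size is unknown, and the net direction of error in the reported count is not assured. The bias in the arm contrast is nil if duration is equal in both arms and modest (about 0.92) in the scenario shown.

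The firmer consequence concerns power. For the planned test, 80% power to detect a halving requires about 71% of control couples to have the outcome.

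**What to change.** 1. Define the laboratory chlamydia/gonorrhoea part of D as month-6 positivity: couples with at least one positive result, compared as a proportion. Do not call it incidence.
2. Report it separately from HIV and syphilis, and from any self-reported diagnoses between visits.
3. Replace the Poisson sentence with the power of the planned chi-square test for the month-6 proportion. State the assumed control proportion, and note that by month 6 both arms have had access to P3.
4. Do not use month-6 positivity as an incidence rate when sizing the efficacy trial. Say in the report that a fall in positivity may reflect shorter infections as well as fewer of them.

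This costs wording and one restated calculation, with no new visits or tests. Data were still being analysed when the article was written, so the change can be made before results are reported. The price is a more modest claim and a less favourable power figure.
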